#### Exclusion criteria:.

(a)History of other neurological disorders (e.g., Parkinson’s disease, tumors, hydrocephalus, or trauma);(b)Cognitive impairment attributable to non-stroke conditions;(c)Significant auditory/visual deficits, aphasia, or uncooperativeness;(d)Pre-stroke cognitive decline.

#### Removal criteria:.

(a)Poor compliance or non-adherence to the protocol;(b)Withdrawal of consent;(c)Incomplete data preventing efficacy evaluation.

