### Study design

This is a single-center, double-blind, randomized controlled exploratory trial. Sixty patients will be randomly assigned to one of four groups (n = 15 per group). The protocol will be reported following Standard Protocol Items: Recommendations for Interventional Trials (SPIRIT) schedule statement(S1 File).Participant enrollment, randomization, assessment, and follow-up schedules are summarized in **Fig 1**.For a detailed visualization of the study workflow, **Fig 2**, which outlines the sequential steps from participant recruitment to final follow-up.

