### Sample size estimation

Prior to study initiation, we will perform sample size estimation using G*Power 3.1.9.7 (Heinrich Heine-Universität Düsseldorf, Düsseldorf, Germany). The primary outcome will be the MoCA score, and the effect-size parameter will be set at Cohen’s f = 0.708, as reported in a peer-reviewed publication [17]. The statistical model will be a linear mixed model testing the group × time interaction. The following settings will be used: power = 0.95, α = 0.05, four groups, three repeated measurements (baseline, post-treatment, and follow-up), and a within-subject correlation of 0.30 (reflecting an expected increase in between-subject variability at follow-up). The software will indicate that a total of 48 participants will be required. Anticipating a 20% dropout rate, we will divide 48 by 0.8 and round up to the nearest multiple of four, resulting in a planned recruitment of 60 participants (15 per group).

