### Statistical methods

#### Clinical data analysis.

Statistical analyses will be conducted using SPSS 26.0, with a two-tailed significance level of p < 0.05. Categorical variables will be presented as frequencies and percentages, and compared using chi-square tests. Continuous variables will be assessed for normality using the Shapiro-Wilk test; normally distributed data will be reported as mean±SD, and non-normally distributed data as median [IQR].For repeated measures (e.g.,cognitive assessments at multiple timepoints), linear mixed models (LMM) will be used to include covariates (e.g., age, baseline scores, education level) and manage missing data. Between-group comparisons at individual timepoints will be conducted using one-way ANOVA for normally distributed data or Kruskal-Wallis tests for non-normal data, with multiple comparisons adjusted using the false discovery rate (FDR) method. Correlations will be analyzed using Pearson’s correlation for normally distributed data and Spearman’s correlation for non-normal data.The primary outcome analysis will be conducted on an intention-to-treat (ITT) basis [26]. Missing data will be addressed using complete case analysis if the missing rate is less than 5%, or multiple imputation if the missing rate is 5% or higher [27].

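### Removal for poor compliance or incomplete data, judged after randomisation, conflicts as written with the intention-to-treat primary analysis and can bypass the multiple-imputation rule

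*Protocol article*

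**What the plan says.** The article has a list of removal criteria, separate from the inclusion and exclusion criteria: "a)Poor compliance or non-adherence to the protocol;(b)Withdrawal of consent;(c)Incomplete data preventing efficacy evaluation". It does not say what a patient is removed from: study treatment, follow-up or the analysis.

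Under Clinical data analysis it says "The primary outcome analysis will be conducted on an intention-to-treat (ITT) basis". The same section handles missing data in two ways. For repeated measures, "linear mixed models (LMM) will be used to include covariates (e.g., age, baseline scores, education level) and manage missing data". A few sentences later, "Missing data will be addressed using complete case analysis if the missing rate is less than 5%, or multiple imputation" once the rate reaches 5%.

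The numbers come from Study design, "Sixty patients will be randomly assigned to one of four groups (n = 15 per group", and from Sample size estimation, "Anticipating a 20% dropout rate, we will divide 48 by 0.8 and round up to the nearest multiple of four".

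**The concern.** Non-adherence and incomplete data are events after randomisation. Taking patients out for them is a completer or per-protocol rule. An intention-to-treat analysis keeps every randomised patient in the allocated arm whatever happens later. If both statements govern the primary analysis, they cannot both be followed.

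Criterion (c) has a second effect. The article's protection against dropout is multiple imputation, triggered by the observed missing rate. If patients whose outcomes are missing are removed before that rate is counted, the trigger may not fire, and the patients for whom imputation was planned are simply left out.

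At stake is the comparison between arms. The Interventions section splits each treatment day in Groups A and B by a 4-hour gap, while C and D receive stimulation and training together. Adherence could therefore differ between the very schedules being compared, and removing non-adherers could select patients differently by arm. With 15 patients per arm, 3 removals are 20% of an arm.

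**Working it through.** **1. The plan's own figure.** Required number before dropout 48, dropout 20% (Sample size estimation): 48 / (1 − 0.20) = 60, or 15 per arm. This matches the article.

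**2. The missing-data rule if everyone stays in.** I count missingness by patient, which is an assumption, because the article does not say how the rate is counted.
- Planned loss: 0.20 × 60 = 12 patients. 12/60 = 20%, which is at or above 5%, so multiple imputation applies and 60 are analysed.
- The complete-case branch needs fewer than 0.05 × 60 = 3 patients missing. It can therefore drop at most 2 (2/60 = 3.3%), leaving at least 58.

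**3. The same rule if criterion (c) acts first.** Suppose r of the 12 patients with missing outcomes are removed before the rate is counted. The apparent rate is then (12 − r) / (60 − r).

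| r removed | patients left | still missing | apparent rate | branch | analysed |
|---|---|---|---|---|---|
| 0 | 60 | 12 | 20.0% | multiple imputation | 60 |
| 9 | 51 | 3 | 5.9% | multiple imputation | 51 |
| 10 | 50 | 2 | 4.0% | complete case | 48 |
| 12 | 48 | 0 | 0% | complete case | 48 |

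The same loss of 12 patients thus gives an analysed number anywhere from 48 to 60, depending on how many are removed and in what order. The article does not fix the order.

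**4. Can the three criteria be read as leaving study procedures only?**
- (a) Poor compliance: possible, since a non-adherent patient could stop procedures and still be followed and analysed. The text does not say so.
- (b) Withdrawal of consent: this does not conflict with intention to treat, provided data already collected are kept.
- (c) Incomplete data: not plausibly. It is worded in terms of judging efficacy, and missing data are no reason to leave treatment. It has effect only on who is analysed.

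**5. What bias could follow.** If a share p of an arm is removed and those removed score d lower on average than those kept, the mean of those kept exceeds the mean of all randomised patients by p × d. The contrast between two arms shifts by p₁d₁ − p₂d₂. The article gives neither p by arm nor d, so the following inputs are assumptions:
- Equal removal with equal d: shift 0.
- 30% removed in A/B against 10% in C/D, d = 0.5 to 1.0 SD: (0.30 − 0.10) × 0.5 = 0.10 SD, up to (0.30 − 0.10) × 1.0 = 0.20 SD, favouring A/B.
- The same removal rates, but those removed score 0.5 to 1.0 SD higher (for example, recovered patients who stop attending): −0.10 to −0.20 SD, against A/B.
- 5% to 20% removed in one arm and none in the other, d = 2 to 4 MoCA points: 0.05 × 2 = 0.1 up to 0.20 × 4 = 0.8 points.

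The sign and size follow entirely from the inputs chosen.

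**The case against.** The conflict is partly inferred. The removal list does not name the analysis set, and the only sentence that sets the primary analysis population says intention to treat. The retention section provides the 3-month follow-up schedule to all patients, not only to adherers. Detailed analysis-set definitions are often left to a statistical analysis plan, which is not shown. The trial calls itself exploratory. On this view one clarifying sentence is enough.

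Much of this stands for criterion (a), and all of it for (b). It does not rescue (c), which makes sense only as exclusion from the efficacy analysis. Nor is the point a complaint about missing detail, since both rules are stated in the article.

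Three stronger readings are tempting, and the document does not support them:
- **That the complete-case rule discards many patients.** It applies only below 5% missing, so at most 2 of 60 counted by patient. At the loss the article expects, its own rule calls for imputation.
- **That 12 patients will be removed.** The 20% is a dropout allowance for the sample size, not a forecast of removals. The figure of 48 is what results if all of that loss were removed first.
- **That the comparison is biased towards A/B.** The 4-hour split is real, but the trial also recruits inpatients, for whom it need not mean a second journey. No removal rates or score deficits are given, and other assumptions make the bias vanish or reverse.

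The two missing-data statements are also less opposed than they look. Imputation followed by a mixed model is a recognised combination, and the section plans single-timepoint tests that the mixed model does not cover. The 5% switch is prespecified and depends on the missing rate, not on arm or outcome values. It is untidy: complete-case analysis would drop partial records that the mixed model could use.

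**Conclusion.** The point holds for criteria (a) and (c). As written they conflict with the stated intention-to-treat primary analysis, most clearly (c), and nothing in the article resolves the conflict. Criterion (c) can also stop the imputation rule from being triggered. If all of the planned 20% loss were removed first, 48 of 60 randomised patients would be analysed, by complete cases; without removal it would be 60, by imputation. This rests on counting missingness by patient and on removal preceding the count, neither of which the article settles.

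The 5% switch is a minor weakness, bounded at 2 of 60 patients. Bias between arms is a possibility that depends on differential removal; no size or direction can be stated from the document. The passages need to be reconciled before analysis.

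**What to change.** 1. State that the primary analysis set is all randomised patients, analysed by allocated arm.
2. State that criteria (a) and (c) remove no one from that set and serve only to define a secondary per-protocol set.
3. State that data collected before withdrawal of consent are kept where consent allows.
4. As a minor point, replace the 5% switch with one prespecified primary approach that uses all available observations, and make the other a sensitivity analysis. The choice is between the linear mixed model on all observed MoCA values and multiple imputation, which also brings in patients with no post-baseline value. A mixed model fitted to post-baseline values alone would leave those patients out, so the choice should be made knowingly.

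The removal list should not be turned into a list of reasons for stopping study treatment. Whether and when treatment stops is left to the investigators.

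The cost is a few sentences of wording, and the article says data collection had not begun at submission. The retention section already provides reminders and remote assessment, but does not mention patients who stop treatment, so following them up may need some extra effort.

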### Randomization

In this study, we’ll use blocked randomization and IBM SPSS Statistics 26.0 (International Business Machines Corporation, Armonk, NY, USA) for a 1:1:1:1 balanced allocation across four groups (pre-, concurrent-, post-training stimulation, and sham control).First, set a fixed random seed (based on the date for reproducibility). With N = 60 and balance needs, define block length as 12 (3 per group) and generate sequences for 5 blocks.Then, use rv.random(1,4) for random integers and sort randomly within blocks.Finally, match sequences with subject numbers (1–60) via match files and sort cases, assigning groups by block and order to control time trend interference.

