### Allocation concealment

To maintain allocation concealment, a pre-generated randomization sequence will be embedded in sequentially numbered, opaque, sealed envelopes. These envelopes will be securely stored and accessed exclusively by designated therapists responsible for stratified randomization of eligible patients into study arms.

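### The generation step, as written, does not ensure three patients per arm in each block of 12 or 15 per arm overall, and fixed blocks with therapist-held envelopes weaken concealment

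*Protocol article*

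**What the plan says.** The Randomization section of the protocol article sets out the procedure step by step. It uses SPSS "for a 1:1:1:1 balanced allocation across four groups (pre-, concurrent-, post-training stimulation, and sham control"). It will then "set a fixed random seed (based on the date for reproducibility") and "define block length as 12 (3 per group) and generate sequences for 5 blocks". The step that creates the random order is to "use rv.random(1,4) for random integers and sort randomly within blocks". The resulting sequences are matched to subject numbers 1 to 60, and groups are assigned by block and order.

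Study design fixes the target: "Sixty patients will be randomly assigned to one of four groups (n = 15 per group").

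Under Allocation concealment, "a pre-generated randomization sequence will be embedded in sequentially numbered, opaque, sealed envelopes". The envelopes are "accessed exclusively by designated therapists responsible for stratified randomization of eligible patients into study arms". The Randomization section names no stratification factor.

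The Blinding section lists participants, outcome assessors and data analysts as blinded. It does not list the therapists.

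**The concern.** A permuted block needs two things: a fixed set of labels with equal numbers per arm, and an ordering of that set in which every arrangement is equally likely. The text states the first as an aim, but the step it gives draws integers from 1 to 4. Four values for four arms look like group codes, and independent draws of group codes do not produce three of each. If the integers are sort keys instead, four values across 12 places must produce ties, and the order then depends on how ties are broken.

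The stakes differ by reading. With free group codes, the arm sizes on which the sample size rests are lost. With tied keys, the sizes hold but the order is biased towards the order of the list. With a proper permuted block, both are sound, but a single fixed and published block length leaves the later places in each block partly predictable. That matters in one centre where the people who open the envelopes also allocate and are not listed as blinded. The timing of treatment also separates the arms: the before-training and after-training arms have a 4-hour interval, while the concurrent and sham arms do not.

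**Working it through.** **Inputs.** Four arms at 1:1:1:1, block length 12, three per arm, five blocks and integers 1 to 4 (Randomization); 60 patients, 15 per arm (Study design); 48 patients before inflation and 20% dropout (Sample size estimation). The documents give neither the seed nor the tie-breaking rule.

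**The plan's own figures.** 5 × 12 = 60 and 5 × 3 = 15 per arm. The rule "we will divide 48 by 0.8 and round up to the nearest multiple of four" gives 48 / 0.8 = 60. Both reproduce, so the block arithmetic is right. The question is whether the generation step achieves it.

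**Reading 1: the integers are group codes, drawn independently.**
- P(3, 3, 3, 3 in a block) = 12! / (3!⁴ × 4¹²) = 369,600 / 16,777,216 = 0.0220.
- P(all five blocks balanced) = 0.0220⁵ ≈ 5.2 × 10⁻⁹.
- P(15 per arm at 60) = 60! / (15!⁴ × 4⁶⁰) = 0.0021.
- Over 60 draws the expected smallest arm is 11.1 and the expected largest 19.1 (simulation).
- The central 95% range for any one arm is 9 to 22.
- The sample size needs 48 / 4 = 12 patients per arm after dropout. The smallest arm starts at 12 or fewer with probability about 0.76 (simulation).
- Sorting afterwards changes the order but not the counts.

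**Reading 2: the integers are sort keys on a list of three per arm.** Assume the list is ordered by arm and ties keep list order. The counts are exact. The first-listed arm takes first place when the smallest of its three keys is no larger than the smallest of the other nine:

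Σₖ [((5−k)/4)³ − ((4−k)/4)³] × ((5−k)/4)⁹, for k = 1 to 4,

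which is 0.5781 + 0.0223 + 0.0002 + (negligible) = 0.60. The last-listed arm needs a strictly smaller key, so the last factor becomes ((4−k)/4)⁹, giving 0.0434 + 0.0006 + (negligible) = 0.044. Both should be 0.25. The pattern reverses at place 12.

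**Reading 3: three fixed labels per arm and a separate, proper random sort.** Balance is exact, and all 369,600 orders of a block are equally likely. What remains is predictability for someone who knows the block length and every earlier allocation:
- An assignment is certain once only one arm is left, so the expected number of certain assignments is the mean length of the final run: 1 + 2/11 + (2/11)(1/10) = 1.2 per block, or 5 × 1.2 = 6 of 60.
- Always guessing the arm with most places left is right 5.29 times in 12, or 44%, against 25% by chance.
- For about 5.1 of the 12 places at least one arm can be ruled out (simulation).

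**Block lengths compared.** In a block of 4, one place in four is certain, and the best guess is right (1/4 + 1/3 + 1/2 + 1) / 4 = 52% of the time. Shorter blocks are therefore worse than 12 if their length is inferred.

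**The case against.** The strongest reply is that the section states blocked randomisation, three per group, and assignment by block and order, and that a journal article condenses software steps. On that view Reading 3 is simply what was meant. This stands as a possibility. It is why the point is that the text does not ensure balance, not that the list is unbalanced. It does not remove the point, because the article chose to spell out the algorithm and the step it gives is not one that enforces its own constraint. The figures for Reading 2 also rest on an arm-ordered list and a stable sort, neither of which is stated.

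Several stronger inferences are tempting but unsupported:
- **That imbalance and predictable block ends both apply.** They belong to different readings. Free group codes have no block end to deduce, and balanced blocks have no imbalance.
- **That the seed can be guessed.** Neither the date nor the seed is disclosed, and a fixed seed for reproducibility is good practice.
- **That selection bias is shown.** Opaque, sealed, numbered envelopes are specified. Under Study setting and recruitment, residents screen inpatients, and the principal investigator does the preliminary screening of outpatients. Therapists pass on interested outpatients, but the text does not say that these are the therapists who hold the envelopes, or that anyone deciding eligibility knows past allocations.
- **That unequal arms would wreck the analysis.** The planned linear mixed model does not need equal arms. For illustrative arms of 11, 14, 16 and 19, the harmonic mean is 4 / (1/11 + 1/14 + 1/16 + 1/19) = 14.4, about 4% below 15. The list is also generated in advance, so an imbalance could be seen before the envelopes are sealed.
- **That the admitted lack of lesion-based stratification, in the Abstract, proves there are no strata.** It does not exclude other factors. The sound contrast is between Allocation concealment and Randomization.

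**Conclusion.** The point holds in limited form and should be corrected. As written, the generation step does not ensure three per arm per block or 15 per arm overall. Of three readings, one gives a balanced block 2.2% of the time, with arms of about 11 to 19 expected. One keeps the counts but gives the first-listed arm first place in about 60% of blocks, if the list is arm-ordered and ties keep list order. One, which needs a step the text does not state, delivers the design.

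Under that last reading a smaller concealment weakness remains: about 6 of 60 assignments certain and a 44% best guess. Both figures are upper limits, since they assume full knowledge of earlier allocations, tracking of block position and optimal guessing. They matter because the allocating therapists hold the envelopes and are not listed as blinded, though the documents do not show that these therapists control enrolment.

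The mention of stratified randomisation has no counterpart in the Randomization section under any reading.

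**What to change.** 1. Replace the generation step: build each block from a list with exactly equal numbers per arm, order it by a continuous uniform random key, and say so. This gives 15 per arm with certainty.
2. Check any list already generated for balance in every block and overall before envelopes are sealed. If envelopes are already in use, have someone outside the trial team make the check and report how the list was actually made.
3. Vary the block lengths and do not disclose them. Avoid blocks of 4. Lengths of 8 and 12 can total 60, for example 3 × 8 + 3 × 12. The article need say only that lengths vary.
4. Have existing staff who neither refer, recruit nor treat hold the list and the envelopes.
5. Reconcile Allocation concealment with Randomization: remove the reference to stratification, or name the factors and describe how blocks are formed within them.

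The cost is a few lines of syntax, some rewording and a reassignment of custody, with no extra patients or staff. Methods and design states that data collection had not begun at submission. If recruitment has since started, the changes to generation and block length can apply only to envelopes not yet used.

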### Allocation concealment

To maintain allocation concealment, a pre-generated randomization sequence will be embedded in sequentially numbered, opaque, sealed envelopes. These envelopes will be securely stored and accessed exclusively by designated therapists responsible for stratified randomization of eligible patients into study arms.

### Blinding

Throughout the trial, participants, outcome assessors, and data analysts will remain blinded to group assignments until final database lock.Unblinding will be permitted solely under emergency circumstances (e.g., serious adverse events). No interim unblinding procedures are required, as all data analyses will be conducted following trial completion.

### Sample size estimation

Prior to study initiation, we will perform sample size estimation using G*Power 3.1.9.7 (Heinrich Heine-Universität Düsseldorf, Düsseldorf, Germany). The primary outcome will be the MoCA score, and the effect-size parameter will be set at Cohen’s f = 0.708, as reported in a peer-reviewed publication [17]. The statistical model will be a linear mixed model testing the group × time interaction. The following settings will be used: power = 0.95, α = 0.05, four groups, three repeated measurements (baseline, post-treatment, and follow-up), and a within-subject correlation of 0.30 (reflecting an expected increase in between-subject variability at follow-up). The software will indicate that a total of 48 participants will be required. Anticipating a 20% dropout rate, we will divide 48 by 0.8 and round up to the nearest multiple of four, resulting in a planned recruitment of 60 participants (15 per group).

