Given the significant gap in research on combined tDCS-CCT intervention strategies, particularly the lack of systematic exploration into the differential effects between simultaneous and sequential intervention modes, this study will investigate the cognitive intervention effects of tDCS in stroke patients undergoing CCT. The primary objective will be to compare efficacy differences across various temporal combinations of tDCS-CCT therapies to identify the optimal synergistic protocol. Rooted in the theoretical framework linking tDCS-mediated cerebral hemodynamic modulation to cognitive enhancement, the study will specifically examine the association between prefrontal cortical oxygen metabolism and cognitive improvement. Functional Near-Infrared Spectroscopy (fNIRS) will be used to dynamically monitor pre- and post-treatment hemodynamic parameters in the prefrontal cortex, aiming to elucidate the neurophysiological mechanisms underlying cognitive recovery through the lens of neurovascular coupling.

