### Interventions

All participants will receive five sessions per week for two weeks, totaling 10 sessions. Adverse events will be monitored during each session, with researchers administering tDCS stimulation according to Brunoni et al.‘s protocol [23] to assess patient discomfort, pain, and any causality related to tDCS. Four treatment groups will be established:

Group A (tDCS-before-CCT): Patients will receive 20 minutes of tDCS, followed by 30 minutes of CCT after a 4-hour interval.Group B (tDCS-after-CCT): Patients will complete 30 minutes of CCT first, then will receive 20 minutes of tDCS after a 4-hour interval.Group C (tDCS-with-CCT): tDCS will be administered concurrently during the last 20 minutes of the 30-minute CCT session.Group D (CCT-only/Sham): Patients will undergo CCT with simultaneous placebo tDCS (sham stimulation).

Prior to the treatment intervention, patients will undergo a baseline assessment to determine eligibility. Enrollment will be based on the Montreal Cognitive Assessment (MoCA) [24]. Assessors will be blinded to group allocation. Post-treatment assessments will be conducted immediately after treatment completion, with follow-up assessments scheduled at 4 and 12 weeks post-treatment.The use of any non-invasive brain stimulation protocols other than those explicitly specified in this study (e.g., transcranial magnetic stimulation [TMS]) is strictly prohibited throughout the research period.

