## Discussion

PSCI remains a significant and unmet challenge in rehabilitation, greatly affecting functional recovery and quality of life. This randomized controlled trial will rigorously evaluate the clinical efficacy of sequential tDCS-CCT interventions for PSCI. Based on previous literature, the sequence of combined interventions may lead to different therapeutic outcomes through distinct neuroplastic mechanisms, as the effects of tDCS are time-dependent, and the impact of stimulation timing exhibits complexity and bidirectionality [28–30]. When the training task is synchronized with the tDCS-induced state of neural excitation, tDCS can optimize neuronal firing synchrony, thereby enhancing synaptic efficiency and cognitive processing through activity-dependent synaptic plasticity. If tDCS is administered prior to CCT, it may initiate neuroplastic networks through a synapse remodeling process similar to LTP; however, the potential interference from homeostatic plasticity mechanisms must be considered. According to the Bienenstock–Cooper–Munro (BCM) theory, the enhancement of postsynaptic activity induced by tDCS increases the modification threshold (MT), thereby reducing the likelihood of LTP and increasing the probability of long-term depression (LTD), which may ultimately impair learning performance [31].In contrast, administering tDCS after training may stabilize newly formed neural connections through activity-dependent synchronization. We hypothesize that the synchronous strategy, by maximizing the immediate induction of LTP, yields the most optimal intervention outcome.

The brain’s high metabolic demand—accounting for 20% of total oxygen consumption despite representing only 2% of body weight—necessitates close monitoring of cerebral hemodynamics [32,33]. Chronic hypoperfusion triggers pathological cascades, including microvascular dysfunction, neuronal injury, and cortical atrophy, ultimately disrupting the functional networks essential for cognition [34]. Functional neuroimaging confirms task-induced neurovascular coupling, wherein activated neurons drive local arteriolar dilation [35,36]. Chen et al.’s tDCS-CCT study demonstrated enhanced cerebrovascular reactivity and regional blood flow, highlighting the utility of HbO as a sensitive biomarker for microvascular changes that predict cognitive recovery.

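### The primary question is which tDCS timing is best, but the stated and powered test is a four-arm test that includes sham and can be significant with no timing difference

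*Protocol article*

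**What the plan says.** The Introduction sets the objective: "The primary objective will be to compare efficacy differences across various temporal combinations of tDCS-CCT therapies to identify the optimal synergistic protocol". The Discussion gives the direction expected: "We hypothesize that the synchronous strategy, by maximizing the immediate induction of LTP, yields the most optimal intervention outcome". Both are questions among groups A (tDCS before training), B (after) and C (concurrent).

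Under Sample size estimation, MoCA is the primary outcome and the powered test is given as "The statistical model will be a linear mixed model testing the group × time interaction", with "power = 0.95, α = 0.05, four groups, three repeated measurements (baseline, post-treatment, and follow-up" among the settings, f = 0.708 and a within-subject correlation of 0.30. The fourth group is D, the sham arm described under Interventions.

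Clinical data analysis adds one-way ANOVA or Kruskal-Wallis tests between groups at each timepoint, "with multiple comparisons adjusted using the false discovery rate (FDR) method". The level is stated "with a two-tailed significance level of p < 0.05". The article names no contrast confined to A, B and C, and does not say which comparisons form the FDR family.

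**The concern.** The objective has the null A = B = C. The stated test has the null A = B = C = sham. The second null is false whenever stimulation at any timing differs from sham, even if timing is irrelevant. A significant result therefore does not answer the trial's main question, and the power claimed for it is not power for that question.

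The same mixing could affect the follow-up comparisons. A false discovery procedure controls the expected share of false claims over its whole family. If true active-versus-sham differences sit in the same family as the timing pairs, rejecting them relaxes the threshold for the timing pairs. With three sham pairs rejected out of six, the timing pairs are judged at 4/6 × 0.05 = 0.033 up to 0.05.

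**Working it through.** **Inputs from the article.** Four arms, 15 per arm planned (12 after the allowed dropout), three measurements, correlation ρ = 0.30, two-sided 0.05, f = 0.708. **Assumed:** A, B and C identical, sham lower by d SD at every post-baseline visit, unit SD, normal outcomes. The article gives no MoCA SD or arm-specific effect, so d is shown as a range.

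**The plan's own figure.** 48/0.8 = 60 is right. The 48 itself is not reproduced by the usual interaction formula λ = f²Nm/(1 − ρ), which needs 14 (16 as a multiple of four). Of the variants tried, only λ = f²N gives 48: 0.708² × 48 = 24.06 on 6 and 88 df, power 0.964. That variant ignores ρ. This is a separate matter, and the point below does not depend on it.

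**Can f = 0.708 come from sham alone?** The arm means deviate from the overall mean by d/4 (three arms) and −3d/4 (sham). The sum of squares is 3d²/16 + 9d²/16 = 0.75d², so f² = 0.75d²/4 = 0.1875d². Setting f = 0.708 gives d = 0.708/√0.1875 = 1.64, with a timing effect of exactly zero.

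**How often is the four-arm test significant with identical timings?** The time pattern (0, 1, 1), once centred, has sum of squares 4/9 + 1/9 + 1/9 = 2/3.

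- Interaction: λ = n × 0.75d² × (2/3)/(1 − 0.30), on 6 and 8(n − 1) df. For n = 15 and d = 0.8, λ = 15 × 0.5 × 0.64/0.70 = 6.86 on 6 and 112 df.
- One-visit ANOVA: λ = n × 0.75d², on 3 and 4(n − 1) df.

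| d (SD) | Interaction, 15 per arm | Interaction, 12 per arm | One-visit ANOVA, 15 per arm |
|---|---|---|---|
| 0.5 | 0.177 | 0.146 | 0.243 |
| 0.8 | 0.435 | 0.344 | 0.570 |
| 1.0 | 0.651 | 0.530 | 0.783 |
| 1.5 | 0.967 | 0.910 | 0.990 |
| 1.64 | 0.987 | 0.955 | 0.997 |

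A 2-df F test on A, B and C rejects in 5% at every d.

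**False timing claims in the follow-up comparisons.** Simulation with 15 per arm, ρ = 0.30, identical timings and Benjamini-Hochberg adjustment. Entries are the percentage of trials with at least one false claim among A-B, A-C and B-C. Three post-treatment visits follow the Interventions section.

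| Procedure | d = 0.5 | 0.8 | 1.0 | 1.64 |
|---|---|---|---|---|
| One visit: four-arm ANOVA, FDR over six pairs | 4 | 5–6 | 6 | 8 |
| One visit: three-arm F, then timing pairs | 5 | 5 | 5 | 5 |
| Three visits, one FDR family of 18 pairs | 5–6 | 9–10 | 13–14 | 18–19 |
| Three visits, one FDR family of nine timing pairs | 4.5–5 | 4.5–5 | 4.5–5 | 4.5–5 |
| Three visits tested separately, six pairs each | 11 | 15–16 | 17–18 | 21–22 |
| Three visits tested separately, three-arm F then timing pairs | 13–14 | 13–14 | 13–14 | 13–14 |

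With no sham effect (d = 0), the one-visit six-pair family gives 2.7%, below the timing-only rate. The last two rows show that most of the error from testing visits separately comes from the repetition and not from sham.

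**Power for a timing claim at one visit, one arm better by 0.8 SD.** The three-arm route has λ = 15 × 0.64 × 2/3 = 6.4 on 2 and 56 df, which gives about 59%. The four-arm ANOVA followed by six-pair FDR gives about 49% if the other two active arms equal sham, and 62% if they also beat sham by 0.8 SD.

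**The case against.** A four-arm omnibus test followed by adjusted comparisons is conventional, and nothing in the article says the omnibus result will itself be read as a timing result. The trial is called exploratory, for which FDR is a defensible choice. The Discussion also aims to evaluate clinical efficacy, so sham belongs in the trial. The membership of the FDR family, and named contrasts, may be in a full protocol or SAP that is not shown. All of this stands, and the undefined family is not raised here as a fault in itself.

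A reader might also infer three stronger claims that the documents do not support.

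- **That FDR raises false timing claims to 11–22% against 5%.** This compares three visits with one, and assumes a family the article does not define. Like for like, the one-visit figures are 4–8% against 5%. With each visit tested separately they are 11–22% against 13–14%. Where the sham effect is small, the four-arm route makes fewer false timing claims.
- **That a tDCS effect alone makes the test significant.** It can, but at d = 0.5 it does so in only about 18% of trials.
- **That the trial expects equal benefit at every timing.** The Discussion expects concurrent stimulation to do best, and warns that stimulation before training may impair learning. Identical timings is a null scenario used to check the test.

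None of this answers the main mismatch. The article does state the primary model test and sizes the trial on it, and that test has a different null from the objective.

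**Conclusion.** The point holds as a mismatch between question and test. The stated four-arm interaction can be significant with no timing difference: about 18%, 44% and 65% of trials for an assumed sham deficit of 0.5, 0.8 and 1.0 SD at 15 per arm and correlation 0.30. The 95% power carries no information about a timing contrast, because f = 0.708 is compatible with a timing effect of zero.

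The effect on false timing claims is conditional. At one visit, under an all-pairs family, there is a modest excess for large sham effects and a reduction for small ones. It becomes substantial (up to about 19% against about 4.5%) only if all visits and pairs form one family and the sham effect is large. These sizes rest on the assumed d, normality, equal correlation between visits and, for the follow-up figures, an inferred family. The mismatch itself rests only on the article's text.

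**What to change.** In Sample size estimation and Clinical data analysis:

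1. Keep all four arms in the mixed model, so that sham still contributes to the error variance.
2. Make the primary test a single 2-df contrast among A, B and C on MoCA, at one named visit or averaged over the post-treatment visits. Either choice also removes the multiplicity from testing each visit.
3. Test A-B, A-C and B-C, each at 0.05, only if that contrast is significant. For three groups this closed procedure holds the familywise error at 5%.
4. Put active-versus-sham comparisons in a separate, separately adjusted family.
5. State that the 95% power refers to the four-arm omnibus test and not to a timing difference.

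The cost is rewording and a few contrast statements, with no extra patients or data. The downside is slightly lower power for a timing claim when all active arms also clearly beat sham: about 59% against 62% for a 0.8 SD advantage of one arm. Power is higher, 59% against 49%, when the other active arms equal sham. The article says data collection had not begun at submission. The change should be made and dated before unblinding, since afterwards it would look data-driven.
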